## Abstract

**Background:**

Kidney transplantation has improved survival and quality of life for patients with end-stage renal disease. Despite excellent short-term results due to better and more potent immunosuppressive drugs, long-term survival of transplanted kidneys has not improved accordingly in the last decades. Consequently there is a strong interest in immunosuppressive regimens that maintain efficacy for the prevention of rejection, whilst preserving renal structure and function. In this respect the infusion of mesenchymal stromal cells (MSCs) may be an interesting immune suppressive strategy. MSCs have immune suppressive properties and actively contribute to tissue repair. In experimental animal studies the combination of mammalian target of rapamycin (mTOR) inhibitor and MSCs was shown to attenuate allo immune responses and to promote allograft tolerance. The current study will test the hypothesis that MSC treatment, in combination with the mTOR inhibitor everolimus, facilitates tacrolimus withdrawal, reduces fibrosis and decreases the incidence of opportunistic infections compared to standard tacrolimus dose.

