**Methods/design:**

70 renal allograft recipients, 18–75 years old, will be included in this Phase II, open label, randomized, non-blinded, prospective, single centre clinical study. Patients in the MSC treated group will receive two doses of autologous bone marrow derived MSCs IV (target 1,5x10^6^, Range 1-2x10^6^ million MSCs per/kg body weight), 7 days apart, 6 and 7 weeks transplantation in combination with everolimus and prednisolone. At the time of the second MSC infusion tacrolimus will be reduced to 50% and completely withdrawn 1 week later. Patients in the control group will receive everolimus, prednisolone and standard dose tacrolimus. The primary end point is to compare fibrosis by quantitative Sirius Red scoring of MSC treated and untreated groups at 6 months compared to 4 weeks post-transplant. Secondary end points include: composite end point efficacy failure (Biopsy Proven Acute Rejection, graft loss or death); renal function and proteinuria; opportunistic infections; immune monitoring and “subclinical” cardiovascular disease groups by assessing echocardiography in the different treatment groups.

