## Background

Kidney transplantation has improved life expectancy and quality of life for patients with end-stage renal failure. However, despite the impressive improvements in short-term outcome parameters due to better and more potent immunosuppressive drugs, the long-term survival of renal allografts has changed little during the past decades [1]. A number of factors, such as quality of the graft, ischemia/reperfusion (I/R) injury, ongoing cellular and humoral alloreactivity and/ or calcineurin inhibitors (CNI) may adversely affect renal structure causing early tubular atrophy and interstitial fibrosis (IF/TA). CNI have been the cornerstone of immunosuppressive therapy for many years, due to their efficacy in preventing acute rejection. However, CNI have nephrotoxic side effects that can directly contribute to renal dysfunction and compromise long-term outcomes. Consequently, there is a clear need for immunosuppressive regimens that maintain efficacy for the prevention of rejection, whilst preserving renal function and structure. The immune regulatory properties of mesenchymal stromal cells (MSCs) in both cellular and antibody mediated inflammatory models have highlighted their potential to regulate the immune response after solid organ transplantation [2]. In addition, MSCs have been shown to ameliorate I/R injury and to exert reparative properties. The administration of MSCs might be an optimal strategy to facilitate CNI withdrawal and to minimize immune suppression. In addition, both MSCs and everolimus might improve cardiovascular status and this strategy might be an opportunity to reduce the toll of cardiovascular disease following kidney transplantation.

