Thirty five of the patients will be included in the everolimus/MSC group and 35 patients in the everolimus/standard dose tacrolimus group (Figure 1, study scheme). All patients will receive steroids and induction treatment with alemtuzumab at day 0 and day 1 (15 mg subcutaneously). BM will be harvested just prior to the renal transplantation only from patients randomised to the MSC treatment group. MSCs will be cultured in the GMP laboratory, as previously described [34]. Patients will receive 2 doses of a target of 1,5×10^6^ MSCs per/kg body weight (range 1-2×10^6^) at weeks 6 and 7 after transplantation. The dose of tacrolimus will be reduced to 50% at the time of the second MSC infusion and completely withdrawn 1 week later. At that time point the patient will receive 15 mg prednisolon. The expected period of patient accrual is approximately 24 months. All study procedures will take place at the LUMC.

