**Figure 1 Fig1:**
[figure not shown]
**Study scheme.** In total 70 patients will be included in the study, 18–75 years old. Patients will be randomised prior to transplantation. Thirty five of these patients will be included in the Certican®/MSC group and 35 patients in the Certican®/standard dose tacrolimus group. All patients will receive steroids (100 mg at day 1 to 3, 50 mg at day 4, 20 mg at day 5 to 15, 15 mg at day 15 to 21, and 10 mg after day 22) and induction treatment with alemtuzumab at day 0 and 1 (15 mg subcutaneously)*. Certican® dose will be 1.5 mg b.i.d. with trough levels between 3 and 8 ng/ml. Tacrolimus will be started orally 3 h before surgery (initial dose 2x5 mg ). In the first 6 weeks target trough levels are aimed at 10 ng/ml (range 8 to 12 ng/ml) for tacrolimus and thereafter 6–8 ng/ml. In the MSC treated group, BM will be harvested just prior to the renal transplantation and MSCs will be cultured in the GMP laboratory. Patients will receive 2 doses of a target of 1,5x10^6^ autologous BM MSCs per/kg body weight IV (range 1-2x10^6^) 7 days apart, 6 and 7 weeks after transplantation. The dose of tacrolimus will be reduced to 50% at the time of the second MSC infusion and completely withdrawn 1 week later. Patients will receive at that time point 15 mg of prednisolone. In all patients a renal biopsy will be performed at 4 weeks and at 6 months and scored according to the Banff criteria.

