Cardiovascular disease exerts a high burden in terms of morbidity and mortality in renal recipients. The annual risk of a cardiovascular event is up to 50-fold higher for a renal recipient compared to the general population [65-67] and over a third of all deaths following kidney transplantation are caused by cardiovascular disease [68,69]. Several studies nowadays focus on the proposed cardio protective effects of everolimus in transplant recipients. In heart transplantation everolimus was significantly more efficacious than mycophenolate mofetil in preventing cardiac allograft vasculopathy (CAV) as measured by intravascular ultrasound (IVUS) among heart-transplant recipients after 1 year [70]. Interestingly, this process might be regulated by T regs, which are expanded after treatment of an mTOR inhibitor [71]. However, mTor inhibitors are also capable to increase the frequency of antigen-specific CD8^+^T cells that differentiated into the memory lineage, thus adequate immune monitoring is of major importance [72]. As MSCs have also been proposed to exert reparative properties in cardiovascular disease, the combination of MSCs and everolimus might be an opportunity to reduce the toll of cardiovascular disease following kidney transplantation.

Taken together, we hypothesize that infusion of MSCs enables CNI withdrawal and provides a novel treatment option for renal recipients with a profound effect on the fibrosis reaction and less side effects than existing immunosuppressive therapies. A positive outcome from MSCs in terms of safety and preservation of renal function and structure would implicate a major advancement for renal transplant recipients.

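### MSC infusion and tacrolimus withdrawal are given only together, so the trial can test the whole strategy but not the effect of MSC that the hypothesis claims

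*Protocol article*

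**What the plan says.** The treatment paragraph that follows the exclusion criteria and the Figure 1 legend describe two arms of 35.

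- **MSC arm.** Cells are infused at weeks 6 and 7, and "The dose of tacrolimus will be reduced to 50% at the time of the second MSC infusion and completely withdrawn 1 week later". Marrow is taken from this arm alone: "BM will be harvested just prior to the renal transplantation only from patients randomised to the MSC treatment group". The same paragraph adds: "At that time point the patient will receive 15 mg prednisolon". The Figure 1 legend repeats this: "Patients will receive at that time point 15 mg of prednisolone". Neither place gives a duration. The common steroid schedule in the legend is 10 mg after day 22.
- **Control arm.** The Abstract (Methods/design) states: "Patients in the control group will receive everolimus, prednisolone and standard dose tacrolimus".

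Everolimus and alemtuzumab are common to both arms. No arm stops tacrolimus without MSC, and none receives MSC while tacrolimus continues.

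The aim is worded in two ways. The Abstract's Discussion asks whether MSC with everolimus can be used for withdrawal and whether that strategy preserves the kidney. The Abstract's Background says MSC treatment with everolimus "facilitates tacrolimus withdrawal, reduces fibrosis and decreases the incidence of opportunistic infections compared to standard tacrolimus dose". The main Discussion closes on the hypothesis that "infusion of MSCs enables CNI withdrawal and provides a novel treatment option for renal recipients with a profound effect on the fibrosis reaction", and then speaks of a positive outcome as coming from MSC. Objectives and endpoints, and the Discussion again, label the primary contrast by MSC treatment status alone.

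**The concern.** The protocol supplies its own rival explanation for a positive result. The Background says "CNI have nephrotoxic side effects that can directly contribute to renal dysfunction and compromise long-term outcomes". The Risk-benefit assessment gives nephrotoxicity as the reason why these drugs are unsuitable in the long term. The Discussion cites a trial of conversion from CNI to everolimus, described without MSC, in which renal function was better for up to three years. Stopping tacrolimus could therefore produce some or all of a fibrosis or GFR difference with no contribution from the cells.

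The enabling claim has the same problem. The Risk-benefit assessment says that alemtuzumab induction and the timing of withdrawal were both chosen to limit rejection. Few rejections in the MSC arm would be what those measures were meant to achieve, with or without MSC. Opportunistic infections are no clearer, because the overall level of immunosuppression changes in the same arm at the same time.

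At stake is the reading of a positive trial. It could be reported as showing an antifibrotic and withdrawal-enabling effect of a cell product when the data cannot distinguish that from the effect of removing a nephrotoxic drug.

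**Working it through.** **1. What the comparison estimates.** Let m be the effect of MSC on mean fibrosis, w that of tacrolimus withdrawal, and s that of any accompanying steroid change. The MSC arm receives all of these and the control arm none. The expected difference between arms is m + w + s (plus any interaction). Two arms identify this sum and none of its parts.

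**2. Can the 4-week biopsy separate them?** No. It is taken before the first infusion (week 6) and before tacrolimus is halved (week 7). Adjusting for it, or analysing change from it, removes baseline differences but leaves m and w combined.

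**3. The plan's own figure.** Inputs from Sample size calculation: means 18% and 14% (difference 4 points), SD 5, two-sided alpha 0.05, power 80%, 25 evaluable per group.

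- Normal approximation: n = 2 × (1.960 + 0.842)² × 5² / 4² = 24.5, rounded up to 25 per group. This reproduces the plan.
- Power at 25 per group is 0.807 by the normal approximation and 0.791 by the exact t-test.

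The 4 points are labelled as the difference for the MSC group, but by step 1 this is the power for the whole package.

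**4. Probability of a significant result if MSC does nothing.** The standard error of the difference is 5 × √(2/25) = 1.414 points. Set m = 0 and let withdrawal, with any steroid effect, lower fibrosis by an assumed amount. The documents give no figure for it, so a range is shown (t-test, 48 degrees of freedom).

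| Assumed fall from withdrawal alone | Fall / SE | P(significant) |
|---|---|---|
| 1 point | 0.71 | 11% |
| 2 points | 1.41 | 28% |
| 3 points | 2.12 | 55% |
| 4 points | 2.83 | 79% |

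The last row equals the power when MSC does all the work, so the test cannot tell the two cases apart. More patients or a different model would not change this.

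**5. Precision of the rejection comparison.** The documents give no expected failure rates, so these are illustrations with 35 per arm. At an assumed 10% in both arms, the 95% half-width is 1.96 × √(2 × 0.1 × 0.9 / 35) = 14.1 points. At an assumed 20% versus 10% it is 1.96 × √((0.16 + 0.09) / 35) = 16.6 points. At these rates, a non-significant difference would not exclude a doubling from 10% to 20%.

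**The case against.** The strongest reply is that the trial compares two regimens and largely says so. The Abstract's Discussion asks about a strategy. Study design describes everolimus with MSC against everolimus with standard tacrolimus. The opening of the main Discussion gives the aim as facilitating CNI withdrawal. The sentence quoted from the end of the Discussion is introduced as a hypothesis in a Phase II protocol and is not a reported conclusion. This stands in part: the randomised comparison is sound for the strategy, and the defect is confined to the places that credit MSC. A hypothesis that no result of the trial could confirm is still badly fixed.

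The protocol also gives a partial reason for having no withdrawal-only arm. The Discussion reports unacceptable rejection when everolimus replaced a CNI from the outset. That evidence concerns avoidance from the start, whereas here tacrolimus is withdrawn later. It helps to explain the design but does not remove the confounding.

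Some stronger readings are tempting but not supported:

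- **Prednisolone as an established third difference.** The 15 mg appears within the description of the MSC arm, without a duration. The contrast with 10 mg is inferred, and nothing in the document links it to fibrosis. The point stands on tacrolimus alone.
- **No success criterion for withdrawal.** The full protocol and analysis plan are not shown and may contain one.
- **The 30% limit as a success rule for efficacy failure.** In the Data safety monitoring committee section, 30% is a rejection rate that leads to study termination. It was not declared as a limit for the composite.
- **A planned misreading of non-significance.** No passage plans to treat a non-significant rejection difference as proof of safety. The protocol names rejection as a risk of withdrawal.

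**Conclusion.** The concern holds as a point of interpretation. MSC and tacrolimus withdrawal are fully confounded by design, the protocol's own text makes withdrawal a credible cause of benefit, and no passage acknowledges this. A difference in fibrosis, renal function or safety cannot be attributed to MSC alone, and the statement that MSC enables withdrawal is not testable.

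On size: with 25 evaluable per arm and SD 5, an inert MSC product would accompany a significant primary result with probability of about 28%, 55% or 79% if withdrawal alone lowered fibrosis by 2, 3 or 4 points. Those falls are assumptions, and the documents do not divide the 4-point difference. The failure rates behind the interval widths are likewise assumed.

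A reader might infer that the trial is invalid. It is not: randomisation supports an unbiased comparison of the whole strategy with everolimus plus standard tacrolimus, and the sample size calculation is not disturbed by this point.

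**What to change.** 1. In the Abstract's Background, Objectives and endpoints, and the Discussion (the primary-endpoint paragraph and the closing hypothesis), restate the hypothesis, primary contrast and permitted conclusion. They should refer to the effect of MSC plus tacrolimus withdrawal, with any accompanying steroid change, on everolimus, versus everolimus plus standard tacrolimus. The Abstract's Discussion already comes close to this.
2. Remove wording that credits the fibrosis, renal function or safety result to MSC alone, and acknowledge that the design cannot separate MSC from withdrawal.
3. Report the between-arm difference in biopsy-proven acute rejection and in efficacy failure with its confidence interval, and state that a non-significant difference will not be taken to show that withdrawal is safe.
4. State whether the 15 mg prednisolone applies only to the MSC arm, and reconcile the treatment paragraph and the Figure 1 legend with the general steroid schedule. Which schedule is right is for the investigators to settle.

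The cost is wording and two reported intervals, with no added patients, arm or procedures. The downside is a more modest claim. Isolating MSC would need a withdrawal-without-MSC comparator. Even if MSC gave the full 4 points, three arms at 70% evaluable would need about 108 patients (25 / 0.7, rounded up to 36, times 3) against the planned 70. That arm is not requested here.

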## Abbreviations

BM: Bone marrow
BPAR: Biopsy proven acute rejection
CAV: Cardiac allograft vasculopathy
CMV: Cytomegalovirus
CNI: Calcineurin inhibitors
CsA: Cyclosporine
DSA: Donor specific antibody
IF/TA: Interstitial fibrosis and tubular atrophy
DSMB: Data safety monitoring board
GFR: Glomerular filtration rate
HSCT: Hematopoietic stem cell transplantation
IVUS: Intravascular ultrasound
I/R: Ischemia reperfusion
MMF: Mycophenolate mofetil
MSCs: Mesenchymal stromal cells
MTOR: Mammalian target of rapamycin
SAE: Serious adverse event
SCR: Subclinical rejection
SR: Sirius red
Tol-DCs: Tolerogenic dendritic cells
